# Effect of physical exercise on spontaneous physical activity energy expenditure and energy intake in overweight adults (the EFECT study): a study protocol for a randomized controlled trial

**DOI:** 10.1186/s13063-018-2445-6

**Published:** 2018-03-07

**Keywords:** Obesity, Exercise training, Physical activity energy expenditure, Energy intake, Compensatory effect

## Abstract

**Background:**

Physical exercise interventions have been extensively advocated for the treatment of obesity; however, clinical trials evaluating the effectiveness of exercise interventions on weight control show controversial results. Compensatory mechanisms through a decrease in energy expenditure and/or an increase in caloric consumption is a possible explanation. Several physiological mechanisms involved in the energy balance could explain compensatory mechanisms, but the influences of physical exercise on these adjustments are still unclear. Therefore, the present trial aims to evaluate the effects of exercise on non-exercise physical activity energy expenditure, energy intake and appetite sensations among active overweight/obese adults, as well as, to investigate hormonal changes associated with physical exercise.

**Methods:**

This study is a randomized controlled trial with parallel, three-group experimental arms. Eighty-one overweight/obese adults will be randomly allocated (1:1:1 ratio) to a vigorous exercise group, moderate exercise group or control group. The trial will be conducted at a military institution and the intervention groups will be submitted to exercise sessions in the evening, three times a week for 65 min, during a 2-week period. The primary outcome will be total spontaneous physical activity energy expenditure during a 2-week period. Secondary outcomes will be caloric intake, appetite sensations and laboratorial biomarkers. Intention-to-treat analysis will be performed using linear mixed-effects models to evaluate the effect of treatment-by-time interaction on primary and secondary outcomes. Data analysis will be performed using SAS 9.3 and statistical significance will be set at *p* < 0.05.

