### Intervention and exercise protocol

For students willing to participate in the study, an exercise treadmill test will be performed prior to the intervention sessions in order to evaluate clinical symptoms and physiological responses during exercise.

The intervention groups (MEG and VEG) will be submitted to exercise sessions in the evening (5–7 p.m.), performed three times a week (Monday, Wednesday and Friday) for 65 min, during a 2-week period. Exercise intensity will be set according to the oxygen uptake reserve (VO_2_R) concept, calculated considering the peak oxygen consumption directly measured during an incremental treadmill test.

Physical exercise sessions will be divided into three phases: warm-up (5 min), training (55 min) and cool-down (5 min). During warm-up and cool-down phases, for both the MEG and the VEG, participants will be instructed to walk at a low intensity.

The training phase of the MEG will consist of four sets of 10 min of walking/running at moderate intensity (40 to 59% VO_2_R), with 5 min walking at low intensity (30 to 39% VO_2_R) for recovery between sets [22]. The training phase of the vigorous exercise group (VEG) will consist of four sets of 10 min of running at vigorous intensity (60 to 89% VO_2_R), with 5 min of walking at low intensity (30 to 39% VO_2_R) for recovery between sets [22].

Participants will self-monitor their target heart rate using a heart-rate monitor Polar FT1 (Polar Electro Oy, Kempele, Finland). In addition, the researchers will monitor all physical exercise sessions to ensure that they will perform the experimental protocol properly.

Participants in the CG will not be submitted to any specific physical training protocol. No specific counseling to change the daily routine of participants during the 15 days will be provided.

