### Sample size

Sample size was calculated based on a mean difference in daily energy expenditure between groups of 110 kcal [23], with a coefficient of variation equal to 1 (standard deviation of 110 kcal) [24]. The sample size required for the study, with an *α* of 0.05 (two-sided), *β* of 0.10 and estimating a drop out of 20%, is 81 adolescents (i.e., 27 in each group) [25].

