### Outcomes

The primary outcome will be total physical activity energy expenditure during the 2-week period. Secondary outcomes will be caloric intake, hungry and satiety sensations and biomarkers (lactate, cortisol, insulin, leptin, acylated ghrelin).

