#### Biochemical and hormonal analyses

Blood and salivary samples will be collected to investigate physiological mechanisms involved in energy expenditure (lactate and cortisol) and food consumption regulation (insulin, leptin and acylated ghrelin), at the first (baseline) and the 15th days of the intervention period, in the morning and after at least 10 h of fasting. Also, salivary cortisol and lactate will be measured after the first and last exercise sessions.

In order to measure salivary cortisol, fasting saliva sample will be collected about an hour after waking up and stored at 4 °C in the Salivette® tube, before eating and brushing the teeth. Participants will bring the salivary sample to the researchers in the same day. The Salivette® tubes will be centrifuged at 1000 × g for 3 min at room temperature and then stored at − 20 °C for later measures, by a commercial ELISA kit. To avoid any confounding factors, the participants will be advised to not do exercise and drink alcohol in the last 24 h, rinse their mouths with water through light mouthwashes immediately prior to collection.

Blood samples will be collected into a 6-ml EDTA K3 vacuum tube with Pefabloc®, 1 mg/mL of blood. The samples will be centrifuged at 3000 × g for 15 min at 4 °C. The serum samples will be aliquoted to identify Eppendorfs for future measurements of insulin, leptin and ghrelin, and stored at – 70 °C. The ghrelin aliquot will be acidified with HCl, to a final concentration of 0.05 N before storage.

Fasting glucose and lactate will be measured using a glucometer (Accu-Chek Active, Roche Diagnostics®, Mannheim, Germany) and a lactate analyzer (Lactate Plus, Nova Biomedical Corporation®, Waltham, MA, USA), respectively. Also, fasting insulin and leptin will be evaluated by a commercial RIA kit. On the other hand, measurements of ghrelin will be performed using a commercial ELISA kit.

The value of the Homeostasis Model Assessment of Insulin Resistance (HOMA-IR) index will be calculated by using the formula:(Fasting insulin (*μ*UI ⋅ mL) × fasting glucose (mmol ⋅ L^− 1^))/22.5 [35]

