### Data analysis

Descriptive analysis for variables of interest consist of means and standard deviation for continuous variables and percentage for categorical variables.

Energy expenditure associated with physical activity will be assessed in the first hour of accelerometer usage, corresponding to the period of the exercise sessions, and over the course of 15 days. Differences between sessions for energy expenditure in the first hour will be performed by using a one-way analysis of variance (ANOVA), followed by a post-hoc Scheffé test. Differences in daily and accumulated physical activity energy expenditure between groups will be performed using linear mixed models that take into account the correlations between repeated measures over time and dropouts. The models will assess the rate of change of the outcomes by the treatment-by-time interaction variable. The covariance structure of the models will be tested and residuals analyses will be performed. To deal with the potential weartime differences between groups, sensitivity analysis will be performed and a “non-wear time” variable will be created and included in the model. Data analysis will be performed using SAS 9.3 (SAS Institute Inc, Cary, NC, USA). Statistical significance will be set at *p* < 0.05 for all analyses.

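### For the fasting biomarkers, the treatment-by-time test in its usual form compares changes from day 1 and makes less use of the pre-exercise baseline than a baseline-adjusted comparison would

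*Protocol article*

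**What the plan says.** The abstract (Methods) names both the model and the test for all outcomes: "linear mixed-effects models to evaluate the effect of treatment-by-time interaction on primary and secondary outcomes". The Data analysis section gives the target of the test: "The models will assess the rate of change of the outcomes by the treatment-by-time interaction variable". The Outcomes section lists the "biomarkers (lactate, cortisol, insulin, leptin, acylated ghrelin" among the secondary outcomes, and hormonal change is a secondary objective.

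Under Biochemical and hormonal analyses, the fasting samples are taken "at the first (baseline) and the 15th days of the intervention period, in the morning and after at least 10 h of fasting". The Intervention section places the "exercise sessions in the evening (5–7 p.m.), performed three times a week (Monday, Wednesday and Friday) for 65 min", so the day-1 morning sample precedes the first session. Cortisol and lactate have further, non-fasting samples: "salivary cortisol and lactate will be measured after the first and last exercise sessions". HOMA-IR is to be calculated but is not listed as an outcome. Allocation is randomised 1:1:1. Neither the abstract nor the Data analysis section mentions a common baseline mean or adjustment for the baseline value.

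**The concern.** A rate of change tested through treatment-by-time suits a long series such as 15 days of accelerometry. Each fasting biomarker has one value before exercise and one after the two weeks. For such a pair, a mixed model that treats both values as responses, with a free day-1 mean in each arm, subtracts the whole baseline difference from the day-15 difference. Randomisation before any exercise means that the arms share one true day-1 mean, and this form of the model does not use that fact.

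Two things follow. The standard error is larger than it need be. And an arm that starts high by chance will tend to appear to fall, through regression to the mean. The trial was sized on a "mean difference in daily energy expenditure between groups of 110 kcal", so nothing in the plan protects the precision of the hormonal comparisons.

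**Working it through.** **Completers per arm.** The plan's own figure comes first. Sample size section: difference 110 kcal, SD 110 kcal, two-sided 0.05, beta 0.10, dropout 20%. n = 2 × (1.960 + 1.282)² × (110/110)² = 21.01 per arm; 21.01/0.80 = 26.27, rounded up to 27; 27 × 3 = 81, as stated. (Rounding to 22 before inflating would give 27.5, hence 28 per arm.) Completers expected: 27 × 0.80 = 21.6, taken as 22 per arm. The documents give no precision or power figure for the biomarkers.

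**Equivalence.** With two time points, complete data and free baseline means, the interaction is the difference in mean change. In one simulated three-arm data set (27 per arm, rho 0.6), the mixed-model interactions were 0.263 and 0.630, each with SE 0.204. A regression of change scores on arm gave the same estimates and SEs. Regressing the day-15 value on arm and day-1 value (ANCOVA) gave SEs of 0.193 and 0.194.

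**Variance.** Take equal SDs at the two days and correlation rho, which is an assumption because the documents give none. Per arm, in units of the squared SD:
- change: 2(1 − rho)
- baseline-adjusted: 1 − rho²
- ratio, adjusted to change: (1 + rho)/2

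**Power.** Noncentral t, pairwise, two-sided 0.05, 22 per arm, with the effect fixed so that the change comparison has 80% power. This needs a noncentrality of 2.868 on 42 df. Adjustment divides that by √((1 + rho)/2) and leaves 41 df.

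| rho | Variance ratio | Noncentrality | Power, adjusted |
|---|---|---|---|
| 0.3 | 0.65 | 3.557 | 93.5% |
| 0.5 | 0.75 | 3.311 | 89.8% |
| 0.7 | 0.85 | 3.110 | 85.9% |
| 0.8 | 0.90 | 3.023 | 83.9% |
| 0.9 | 0.95 | 2.942 | 81.9% |

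A simulation of 4,000 trials at rho 0.5 agreed: 81.2% for change and 90.2% for ANCOVA.

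**Limit of the formula.** It ignores the cost of estimating the slope. Simulation with 22 per arm (40,000 trials) gave variance ratios of 0.76 at rho 0.5, 0.87 at 0.7, 0.97 at 0.9, 1.00 at 0.95 and 1.02 at 0.98. The advantage therefore vanishes, and reverses slightly, at very high correlation.

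**Chance imbalance.** A baseline difference D between two arms carries into the change comparison as −(1 − rho)D. With 22 per arm, the SD of a chance D is √(2/22) = 0.30 SD, so the typical shift is 0.5 × 0.30 = 0.15 SD at rho 0.5 and 0.1 × 0.30 = 0.03 SD at rho 0.9. Over 4,000 simulated two-arm trials (27 per arm, rho 0.6), the correlation of the estimate with the chance baseline difference was −0.44 for change and 0.00 for ANCOVA. The SD of the estimate was 0.242 and 0.219.

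**The case against.** The strongest objection is that the free-baseline model is inferred. The article does not mention change scores, and a model with a common baseline and a treatment-by-day-15 term is itself a treatment-by-time interaction in a linear mixed model. That stands as far as it goes: the quoted sentences permit the better model. But a rate of change by treatment-by-time points to the conventional form, and nothing in the text points to the constrained one.

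A second objection is that covariates are commonly left to an SAP. That would answer a complaint about a missing covariate list, but here the test itself is named twice. Listing baseline as a covariate while day 1 also stays in the response would leave the interaction unchanged.

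Third, the Data analysis section introduces the mixed models for physical activity energy expenditure. The link to biomarkers rests on the abstract and on that section's general reference to the outcomes. This is fair, but the abstract is explicit and no other biomarker model is given.

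A reader might also infer more than the documents support:
- That the biomarker results would be biased or the type I error inflated. They would not: the difference in change is unbiased over randomisation, and the loss is one of precision and of conditional dependence on imbalance.
- That adjustment always wins. It does not at very high rho in samples of this size.
- That the two-point equivalence covers all cortisol and lactate data. It covers only their fasting pair.
- That HOMA-IR is an affected outcome. It is not on the list of outcomes.

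**Conclusion.** The point holds as one of efficiency in secondary outcomes: insulin, leptin, acylated ghrelin, and the fasting cortisol and lactate pair. Read in its usual form, the named test gives up about 13 points of power at rho 0.3, 10 at 0.5, 6 at 0.7 and 2 at 0.9, measured from 80% with 22 completers per arm. It also lets chance baseline differences move the estimate.

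The size rests on three assumptions: a correlation that the documents do not give, equal SDs at the two days, and free baseline means per arm. With dropout, the mixed-model interaction is close to a complete-case change analysis but not identical. The primary outcome and the total of 81 are unaffected. The change is worth making because it uses data already collected.

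**What to change.** For each fasting biomarker, keep the linear mixed model on the day-1 and day-15 values but constrain the arms to one common day-1 mean: include time and treatment-by-day-15 terms and no treatment effect at day 1. State that the test is of the day-15 difference between arms. This retains participants who have only a baseline sample and so fits the intention-to-treat plan.

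ANCOVA of the day-15 value with the day-1 value as covariate is the complete-case counterpart. The two are not identical under the 20% dropout that the plan expects, so the plan should say which is the main analysis. Apply the same model to HOMA-IR if it is analysed, and handle the post-session cortisol and lactate samples separately.

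The cost is a sentence or two of analysis wording, with no new data. The estimate no longer reads as a raw difference in change, and the gain is negligible at rho of about 0.9 or above.

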**Discussion:**

The results of the present study will help to understand the effect of physical exercise training on subsequent non-exercise physical activity, appetite and energy intake as well as understand the physiological mechanisms underlying a possible compensatory phenomenon, supporting the development of more effective interventions for prevention and treatment of obesity.

**Trial registration:**

Physical Exercise and Energy Balance trial registry, trial registration number: NCT 03138187. Registered on 30 April 2017.

**Electronic supplementary material:**

The online version of this article (10.1186/s13063-018-2445-6) contains supplementary material, which is available to authorized users.

## Background

Obesity is an important multifactorial condition associated with an increased risk of many chronic diseases and high mortality rates [1]. The prevalence of obesity has been increasing over the last decades, mainly due to an imbalance between energy intake and expenditure during an extended time period [2, 3].

Physical exercise interventions have been extensively advocated for the treatment of obesity [2]. The rationale is to facilitate weight loss, generating a negative energy balance by increasing total energy expenditure. However, some clinical trials evaluating the effectiveness of exercise interventions on weight control did not confirm this hypothesis [4–6].

The small or even null effect of exercise on weight management observed in some studies could be explained by the lower energy deficit actually induced by exercise training in comparison to those theoretically predicted. According to the activitystat hypothesis [7], an increase in physical activity levels in one moment is compensated by decreasing physical activities in another moment in order to maintain an overall physical activity set point [8, 9]. This compensatory energy expenditure effect was observed by some [10, 11] but not confirmed by others authors [12].

Another important aspect that could wane the influence of exercise on weight loss is the potential increase in food consumption as a compensatory effect of an exercise-induced energy expenditure [13]. Some studies have demonstrated that exercise training can increase hunger and promote overfeeding, decreasing the expected negative energy balance and making weight loss more difficult [14, 15]. However, other studies showed that appetite and caloric intake are decreased or unchanged after physical activities [16, 17]. The conflicting results observed in the academic literature may be related to the heterogeneity of the studies, in which large methodological differences (study population, exercise protocols, evaluated variables) are observed.

Several physiological mechanisms, particularly hormonal, are involved in the energy expenditure and intake regulation and can explain these behavioral compensatory mechanisms [18, 19]. However, the existing interactions and the influence of physical exercise on these adjustments are still unclear. Therefore, it is necessary to better understand the relationship between physical exercise and energy expenditure, as well as the possible interdependence between energy expenditure and food consumption and the hormonal regulatory mechanisms related to energy balance in overweight individuals. The influence of different exercise intensities on energy expenditure and food intake should also be investigated. The EFECT study, which stands for “Physical Exercise and Compensatory Effects” in Portuguese, is designed to address this gap in the academic literature. For the main outcome, we hypothesize that a greater reduction on spontaneous physical activity energy expenditure will be observed in the vigorous exercise group (VEG) after the 15-day follow-up.

## Objectives

### Primary objective

To evaluate the effect of different exercise intensities on spontaneous physical activity energy expenditure and energy intake

### Secondary objectives

To evaluate hunger/satiety associated with exercise intensityTo investigate hormonal changes associated with exercise intensity

## Methods

### Study design

A randomized controlled trial, designed to evaluate the effect of structured physical exercise sessions on the spontaneous physical activity energy expenditure and caloric intake in overweight adults. The design employs parallel, three-group experimental arms: (1) a moderate exercise group (MEG); (2) a vigorous exercise group (VEG); and a control group (CG) without physical exercise sessions. The planned flow diagram of this trial is presented in Fig. 1. The protocol is reported according to the Standard Protocol Items: Recommendations for Interventional Trials (Fig. 2 SPIRIT diagram and Additional file 1: SPIRIT checklist).

**Fig. 1 Fig1:**
[figure not shown]
Planned flow diagram

**Fig. 2 Fig2:**
[figure not shown]
SPIRIT diagram

### Study setting

The trial will be conducted at the Naval Academy (Brazilian Navy, Rio de Janeiro, Brazil) during the school year of 2017. This military academic institution allows a very controlled experimental condition to conduct this study. In this institution, approximately 900 students, aged 18 to 24 years, undergo a military training during a period of 4 years. The institution works on boarding from Monday to Friday and during the weekend students are free to go home.

During the weekdays, all students have the same routine at school: they wake up at 6 a.m., attend academic classes in the morning and physical exercise classes in the afternoon. The school offers three basic meals: breakfast at 6 a.m., lunch at 12 p.m. and dinner at 7 p.m. At 10 p.m. students must go to their bedrooms to sleep.

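### The expenditure totals meant to show spontaneous activity include the school's timetabled exercise classes, so lower effort in class would be read as lower spontaneous activity

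*Protocol article*

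**What the plan says.** The primary objective is "To evaluate the effect of different exercise intensities on spontaneous physical activity energy expenditure and energy intake". The Abstract frames the question as non-exercise expenditure and names total spontaneous expenditure over two weeks as the primary outcome. The hypothesis at the end of the Background also concerns spontaneous expenditure. The Outcomes section leaves out the word spontaneous and refers to total physical activity expenditure.

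Under Study setting, the weekday routine is the same for all students, who "attend academic classes in the morning and physical exercise classes in the afternoon". Under Intervention and exercise protocol, the two exercise arms "will be submitted to exercise sessions in the evening (5–7 p.m.), performed three times a week (Monday, Wednesday and Friday) for 65 min". For controls, "Participants in the CG will not be submitted to any specific physical training protocol", and "No specific counseling to change the daily routine of participants during the 15 days will be provided".

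The accelerometer is worn for 15 consecutive days and taken off only for bathing and water-based activity. The Data analysis section names two windows: the first hour of use, matched to the exercise session, and the full 15 days. For the latter, "Differences in daily and accumulated physical activity energy expenditure between groups will be performed using linear mixed models". A sensitivity analysis deals with non-wear time. No window isolates time outside the school classes.

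**The concern.** Expenditure in a timetabled class is not spontaneous, yet it sits inside the total that is to answer a question about spontaneous activity. Two consequences follow.

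- **Interpretation.** Students who train hard in the evening may ease off in the school class. That is a form of compensation, but a different one from moving less in free time. The planned totals merge the two and would attribute both to spontaneous activity.
- **Precision.** If students differ in how hard they work in class, that variation enters the outcome and may weaken the comparison.

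The trial's stated purpose is to understand how compensation arises. An outcome that cannot show where in the day it occurs serves that purpose less well than the recorded data allow.

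**Working it through.** **1. What the total contains.** Write a student's accumulated expenditure as Y = D + C + S, where D is discretionary time, C the school classes and S the trial sessions. The between-arm difference is

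ΔY = ΔD + ΔC + ΔS.

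The hypothesis is about ΔD. The planned model estimates ΔY.

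- If classes cost the same on average in each arm, ΔC = 0 and the classes drop out. Randomisation and a common routine make this the natural starting point.
- If an exercise arm eases off in class, ΔC < 0, and the analysis cannot tell this from ΔD < 0.
- The documents do not say whether the 5–7 p.m. sessions stand in for the school class on session days. If they did, ΔC would differ by arm by design.
- ΔS arises in the exercise arms only. It is a separate matter, but any definition of the spontaneous component must deal with it too.

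**2. How class effort would enter the daily mean.** The Food consumption section makes day 2 a Tuesday and day 15 a Monday, so day 1 is a Monday. Days 2–14 hold 9 weekdays and 4 weekend days. With one class per weekday (assumed), a reduction of c kcal per class lowers the mean daily total by 9c/13 = 0.69c. None of it would be spontaneous. The documents give no value for c.

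**3. The plan's sample size, reproduced.** Inputs from the Sample size section: difference 110 kcal, SD 110 kcal, two-sided α 0.05, β 0.10, dropout 20%.

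n per arm = 2 × (1.960 + 1.282)² × (110/110)² = 21.01; 21.01/0.8 = 26.3, rounded up to 27; 3 × 27 = 81. This matches.

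Completers: 27 × 0.8 = 21.6, taken as 22 per arm. Power = Φ[110/(110 × √(2/22)) − 1.960] = Φ(1.357) = 0.91.

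**4. Added variance, by assumption.** Suppose class effort adds an independent between-student SD of s, and the difference stays at 110 kcal. The total SD is √(110² + s²).

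| Assumed s (kcal) | Total SD (kcal) | Power, 22 per arm |
|---|---|---|
| 0 | 110.0 | 0.91 |
| 30 | 114.0 | 0.89 |
| 55 | 123.0 | 0.84 |
| 80 | 136.0 | 0.77 |
| 110 | 155.6 | 0.65 |

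No value of s stands in the documents. Nor do they say whether the planning SD already includes class activity. If students who work hard in class rest more afterwards, the covariance is negative and the loss is smaller or absent.

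**The case against.** Much of the opposing case stands, and it rules out several stronger readings.

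- **A reader might infer that the classes dilute the between-arm difference.** They do not. A load common to all arms cancels, as step 1 of the working shows, and with no variation between students it leaves power unchanged as well.
- **A reader might infer that the target difference is out of reach in so regulated a day.** If weekday free time is only 7–10 p.m., it is 3 of 16 waking hours (19%). At an assumed 75–95 kg and 1.3–1.8 METs, 110 kcal would then be about half to more than all of evening activity expenditure. That leaves out the weekends, although the target is a daily mean. With 16 free hours assumed on weekend days, free time is (9 × 3 + 4 × 16)/(13 × 16) = 91/208 = 44%, or 7 h a day. Activity expenditure above rest, (MET − 1) × kg × 7, is then about 158 to 532 kcal, and 110 kcal is 21% to 70% of it. The weights and METs are not in the documents, class length is not given, and compensation within class is ignored. No claim of infeasibility is supported.
- **A reader might infer that the control arm is misdescribed.** The phrase "a control group (CG) without physical exercise sessions" plainly refers to the trial's own sessions. The Abstract calls the participants active, and the Study setting section discloses the classes.
- **A reader might infer that timetabled activity differs by school grade.** No section says so; the routine is described as common to all.

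Two further points carry weight. The activitystat hypothesis in the Background concerns overall activity, so the whole-day total is a legitimate quantity and easing off in class is real compensation. This is a reason to keep the total and report class time, not to leave them merged under the name spontaneous. Also, re-windowing creates no extra free time: a null result could still reflect limited opportunity.

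Finally, time filters may be left to a fuller document. But this article does state its analysis windows, and those windows do not match its question.

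**Conclusion.** The point holds in a limited form. The stated question is about spontaneous activity, while the analysed totals cover the whole day, including exercise classes that every arm attends on weekdays. No bias in the between-arm difference follows from a common class load. What follows is that reduced class effort would be reported as reduced spontaneous activity, and that variation in class effort may cost some precision.

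The size of either effect cannot be computed from the documents. The power figures of 0.84 to 0.77 rest on an assumed, independent added SD of 55 to 80 kcal and show sensitivity only. The conclusion also assumes that the classes continued during follow-up, which is the natural reading because the routine is left unchanged and no section says otherwise.

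**What to change.** Obtain the school timetable and split the accelerometer record, which is stored in 5-second epochs. Report by arm:

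1. the spontaneous component: expenditure outside scheduled exercise classes and outside the 5–7 p.m. window, removing the same clock window in all three arms on session days;
2. class-period expenditure, as a separate possible component of compensation;
3. the whole-day total, as supportive.

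Give weekday and weekend estimates for each. Use one name for the outcome in the Abstract, Objectives and Outcomes sections. State the conclusion as the effect of exercise added to the school's existing training.

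The cost is small: analysis wording and time filters, with no new measurements on participants. The downsides are that the timetable must be obtained and that class-time compensation is read from a second estimate.
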